### III. Study Design:

- A. Provide an overview of your study design and methods. The study design must relate to your stated aims/objectives. Details will be requested later. If your study also involves analysis of existing data, please complete Section XI, “Secondary Data Analysis of Existing Data” in the last part of this research plan. If your study ONLY involves analysis of existing data, please use the research plan template for secondary data analysis (JHSPH IRB Research Plan for Secondary Data Analysis of Existing Data/Specimens).

The study is a randomized controlled trial at the individual level that uses a stepped wedge design to assess the peer-mentoring/AIDSTAR-One toolkit intervention. The study team will test a six-month peer-mentoring program among 144 YLHIV in an intervention arm compared to 144 YLHIV in a comparison arm. Participants for the RCT will be consecutively selected from two hospitals -- Arthur Davison Children’s Hospital (ADCH) and Ndola Teaching Hospital (NTH) – and two primary care clinics (PCCs) – Twapia Clinic and Lubuto Clinic. The participating facilities were purposively selected because they represent different models of care. ADCH is a hospital for children and serves older youth who should ultimately transition to adult care. In contrast, NTH and the two primary care clinics are essentially adult HIV care settings. While they were not designed to initially serve HIV positive adolescents, they continue to experience a growth in the number of enrolled adolescents. The PCCs were purposively selected based on their high ALHIV patient populations, designated ART center status, and proximity to other study sites.

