#### AIM 1 Calculations

The sample size calculation is based on recent data on viral load suppression. This intervention is designed to support adolescents to manage their HIV as they transition into adulthood to achieve healthy outcomes, with viral suppression being the strongest outcome measure that is feasible. Viral suppression is a key health outcome we aim to achieve and maintain through the transition process and is of particular importance as ADCH program data has indicated that only 50% of 15-19 year olds are virally suppressed, with 50% having viral loads of 1,000 copies/ml or greater. With group sample sizes of 144, we will have over 85% power to detect a difference of 20% (an increase from 50% to

---

 Data are from ADCH’s routing VL screening, which is being conducted among adolescents who had been on cART for a minimum of 6 months, although many have been on cART for years.

70%) between the proportions virally suppressed in the intervention versus the control arms at the six-month data collection point, with Type 1 error of 5%, and 20% loss to follow-up. The team will also explore differences in self-reported adherence among the two study arms, with adherence assessed using a 30-day and 48-hour treatment gap measures that we have used in our previous research. Adherence is a proxy for achieving viral suppression. Adherence is also one of the toolkit module topics and maintaining adherence is a criterion for transition in the readiness to transition checklist.

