#### **AIM 1:**

We will recruit participants consecutively as they attend the HIV care and treatment clinics, aiming to achieve diverse enrollment based on sex and age. When possible, SMART Care appointment lists will be made available by clinic staff to assist the study team in anticipating the numbers of potentially eligible youth scheduled to be seen at each study site (SMART Care is the electronic medical record system). Trained clinic staff and study staff members will work in tandem to recruit eligible participants using a recruitment script. Clinic staff will have access to each patient's medical chart and will work to ensure that patients who fall within the age range and are aware of their HIV-positive status are approached. They will then refer interested youth to a study staff member. The study team has had success recruiting adolescents using these methods in their previous research in Zambia. Once enrolled the study team member will place a sticker on a back page of the youth's medical file (a page not typically used by clinic staff and not visible from outside the folder) to indicate participation in the study. This sticker will help ensure the study team does not enroll the same person twice and also ensure that the test results are placed in the correct file. Ultimately, we plan to enroll an estimated 144 participants from ADCH, a pediatric clinical setting, and 144 from three adult settings: NTH, Lubuto Clinic, and Twapia Clinic.

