### **Aim 1 & Sub-Aim 1A Quantitative Analyses**

The primary analysis to assess impact will use generalized estimating equation (GEE) (22) to compare the intervention to the comparison arm on VL suppression. This process will also be used to examine other key outcomes over time, such as self-reported medication adherence and internalized stigma.

This approach accounts for within subject correlations due to repeated measures. We will use GEE models with appropriate link functions (e.g., identity for continuous data, logit for binary data) and variance functions (e.g., identity for continuous data, logit for binary data) and variance functions (e.g., normal for continuous data, binomial for binary data). Unstructured working correlation matrices will be used in all models. The primary outcome will be cART adherence as measured by viral load suppression  $\leq 1,000$  copies/mL. In the stratified analysis (aims 1A), the models described above will be fit separately to two sub-samples of study participants – those participants who started the intervention in a pediatric care setting (i.e. ADCH) and those participants who started the intervention in an adult care setting (i.e. NTH, Twapia Clinic, and Lubuto Clinic). We will also examine pre- and post-intervention effects, and if outcomes change over time, at the 6-month and 12-month follow-ups. Secondary outcomes will include adolescents' transition status, including how many adolescents physically transitioned to adult care from the children's hospital.

Descriptive statistical methods will be used to assess the feasibility and acceptability of the intervention. The study team will also analyze attendance and the reasons for missed sessions. Together these data will provide valuable information on the feasibility of the intervention and participant exposure to intervention elements.

Finally, secondary data analyses will be carried out on participants' reported experiences of violence victimization. Descriptive statistics will be used to obtain weighted estimates of the youth's

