lifetime and past-year prevalence of physical, psychological, and sexual violence victimization, with percentages and 95% confidence intervals. Logistic regression will be conducted to examine associations between youth's violence victimization and VL suppression, with GEE models to account for the potential correlations between youth's responses from the same clinic. Associations between violence victimization and VL suppression will further be assessed using propensity scores. Such analyses will shed light on the prevalence of violence victimization and its relationship with VL within a population of youth living with HIV in Zambia, which will inform the potential integration of violence-focused content into the intervention.

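### The violence and viral-suppression analysis clusters GEE on only four clinics, too few for the usual robust test; clinic should enter as a fixed factor

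*Protocol*

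**What the plan says.** The data analysis plan (Protocol, section V.C.4, Aim 1 & Sub-Aim 1A Quantitative Analyses) contains two separate uses of GEE.

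- **Trial outcomes.** The first paragraphs describe GEE for viral suppression, adherence and stigma over the study visits. The cluster is the participant: "This approach accounts for within subject correlations due to repeated measures". In the same paragraph stands "Unstructured working correlation matrices will be used in all models".
- **Violence analysis.** Two paragraphs later, "secondary data analyses will be carried out on participants' reported experiences of violence victimization". The association with viral suppression is to be examined by logistic regression, "with GEE models to account for the potential correlations between youth's responses from the same clinic", and also with propensity scores. Here the cluster is the clinic. No working correlation, variance estimator, reference distribution or small-sample correction is named.

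The number of clinics is fixed elsewhere. Section III.A lists two hospitals "and two primary care clinics (PCCs) – Twapia Clinic and Lubuto Clinic", so there are four. Section V.A (Recruitment Process, AIM 1) plans 144 participants at the children's hospital and "144 from three adult settings: NTH, Lubuto Clinic, and Twapia Clinic". How those 144 divide among the three adult sites is not stated.

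**The concern.** GEE protects against a wrongly specified within-cluster correlation through its sandwich variance. That variance is an average over clusters and is reliable only when there are many of them. With four clusters, one holding half the sample, it tends to be too small, and a normal critical value takes no account of how poorly it is estimated. The usual result is intervals that are too narrow and too many significant associations.

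The Protocol says that these associations will inform whether violence-focused content might be added to the intervention. Physical, psychological and sexual violence are all in view, so there are several chances for a spurious finding to enter that discussion.

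**Working it through.** **The plan's own figures.** The Protocol gives no error rate or precision for the violence analysis. Its Aim 1 power statement belongs to another comparison, but it reproduces. With 144 × 0.8 = 115 per arm and 50% against 70%, the pooled standard error is √(2 × 0.6 × 0.4 / 115) = 0.0646 and the unpooled one is √((0.25 + 0.21) / 115) = 0.0632. Then (0.20 − 1.96 × 0.0646) / 0.0632 = 1.16, which is a power of 87.7%, consistent with the stated figure of over 85%. Nothing below changes it.

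**Inputs from the Protocol.** Four clusters; 288 participants; 144 at the children's hospital and 144 over three sites; suppression of 50% (section III.B: "only 50% of 15-19 year olds are virally suppressed"); 5% type I error, taken as two-sided because the side is not stated.

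**Assumptions, since the Protocol gives no figures.**
- Clinic sizes 144/48/48/48, with 144/80/32/32 and 72 in each clinic as sensitivity cases.
- Violence prevalence 30% to 50%.
- Intraclass correlation of suppression by clinic (ICC) 0 to 0.05, generated by a clinic effect on the logit scale with variance ICC/(1 − ICC) × π²/3.
- Between-clinic standard deviation of violence 0 to 0.3 on the logit scale.
- No true association between violence and suppression.

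**A rough guide before simulating.** If the only fault were that a variance with 4 − 1 = 3 degrees of freedom is treated as known, the true error would be P(|t₃| > 1.96) = 1 − (2/π)[arctan(1.96/√3) + (1.96/√3)/(1 + 1.96²/3)] = 1 − (2/π)(0.847 + 0.496) = 0.145. Downward bias of the sandwich variance adds to this. In one run with sizes 144/48/48/48, the mean robust standard error was 0.71 to 0.75 of the true standard deviation.

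**Simulation.** Logistic GEE by clinic with independence or exchangeable working correlation, 1,500 to 3,000 data sets per scenario. The Monte Carlo standard error at 5% with 1,500 runs is √(0.05 × 0.95 / 1500) = 0.6 percentage points.

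| Test of the violence coefficient | Rejection of a true null at nominal 5% |
|---|---|
| Robust SE, normal reference, 144/48/48/48 | about 21% to 24% |
| Robust SE, normal reference, 144/80/32/32 | about 22% |
| Robust SE, normal reference, 72 in each | about 17% to 21% |
| Robust SE, t on 3 degrees of freedom | about 5% to 11% |
| Model-based SE, exchangeable GEE | about 5% to 6% |
| Logistic regression, clinic as fixed factor | about 3.5% to 6% |

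The corresponding nominal 95% robust intervals would cover the true null value in only 100 − 24 = 76% to 100 − 17 = 83% of cases. The inflation is about the same at an intraclass correlation of 0 as at 0.05. It therefore comes from the number of clusters, not from any assumed clinic effect.

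**Unstructured correlation.** For a person with three visits it has 3 × 2 / 2 = 3 parameters, which is routine. At clinic level, a cluster of 144 would need 144 × 143 / 2 = 10,296 correlations, and even one of 48 would need 48 × 47 / 2 = 1,128, all from four clusters. A trial fit failed with non-finite values.

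**The case against.** The best reply is that the Protocol form asks only for a brief analysis plan. The variance estimator, reference distribution and small-sample correction of a secondary model are normally settled in the statistical analysis plan, which is not shown. What the Protocol does fix, GEE by clinic, can be run at close to the nominal level. This stands: the 17% to 24% applies to one common way of carrying out the plan and is not a property of the plan as written. What remains is that the Protocol itself chose a clustering unit with four members. Model-based standard errors keep their level only if the working correlation is about right, and under an exchangeable structure that correlation would itself be estimated from four clinics.

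Some stronger readings are tempting but are not supported.

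- **That the violence model cannot be fitted.** The sentence on unstructured matrices sits in the paragraph on within-subject repeated measures. The violence analysis comes later, with its own method and no named working correlation. Only a literal reading of the sentence's scope carries it over, so this is an ambiguity of wording.
- **That the plan yields a 20% false-positive rate outright.** That rate belongs to an independence or exchangeable model with an uncorrected sandwich error and a normal reference. It cannot also describe an unstructured model that fails to fit.
- **That the robust covariance is singular and therefore useless.** With four clusters its rank is at most three, which blocks joint tests of more than three parameters. A standard error for the single violence coefficient is still available, and the Protocol lists no covariates for this model.
- **That these results decide the intervention's content.** The Protocol says only that they will inform a possible addition. Propensity-score analyses and interviews sampled on violence experience bear on the same question.

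**Conclusion.** The point holds in limited form. Clustering on four clinics is a poor choice for this association. If it is run as GEE commonly is, with an uncorrected robust standard error and a normal reference, the type I error is about 17% to 24% in place of 5%. The size rests on the assumed clinic splits, violence prevalence and clinic effects listed above, and it changes little across them. With model-based standard errors or a t reference on 3 degrees of freedom the error is about 5% to 11%, and the Protocol neither requires nor excludes these. The analysis is secondary and observational. The randomised Aim 1 comparison, whose repeated measures are clustered on participant, is untouched.

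**What to change.** In the violence paragraph of section V.C.4, replace clinic-clustered GEE with logistic regression that includes clinic as a fixed factor (three indicators) and uses model-based standard errors. Site is already a randomisation stratum, so the variable is at hand. The cost is one sentence and three degrees of freedom, and the odds ratio is then read as a within-clinic association. If more than one visit per participant enters the model, cluster on participant and keep clinic as a factor.

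If clinic-clustered GEE is retained, state a variance method and reference distribution suited to four clusters; of the alternatives checked, t on 3 degrees of freedom only partly removes the inflation.

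Separately, restrict the sentence on unstructured working correlation to the person-level repeated-measures models. This is a wording clarification and changes no analysis of the trial outcomes.

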## **Aim 2 Qualitative Analysis**

A content analysis approach will be utilized for the qualitative analysis. To facilitate this process, all IDIs will be audio-recorded with participant permission, transcribed, translated, and coded with a qualitative software package, such as Nvivo. These codes will help identify common themes and concepts across interviews (e.g., favorite/least favorite elements of the peer-mentoring intervention). The study team will develop initial codes (e.g., positive perspectives, negative perspectives) but will also work together to identify and build upon themes identified as salient in the text.

### **5. Answer the following if they are relevant to your study design:**

- A. If the study has different arms, explain the process for assigning participants (intervention/control, case/control), including the sequence and timing of the assignment.

#### *Randomization description*

After baseline data collection, study participants will be randomized in 1:1 allocation ratio to receive either peer-mentoring intervention or usual care. Stratified randomly permuted block randomization (block sizes 4 and 6) will be used to generate the randomization scheme. Blocking will facilitate balanced allocation between the intervention arms, and random block size will reduce predictability of the group assignment. Randomization will be stratified by site and by gender, within site, for a total of 16 strata. Random allocation list will be generated, separately for each stratum, using 'ralloc' command (23) in STATA statistical software (24). The total sample size is 288 adolescents, but 380 random allocations are created (on average 38 per stratum) to account for potential allocation mistakes or discontinuations. If males are difficult to recruit more random allocations may be generated for females to make sure to reach the total sample size needed.

#### *Allocation Concealment*

Random allocation will be concealed from the study team by the use of opaque envelopes that contain the stratum designation (e.g. male, 15-24, ADCH), a sequential number, and, on the inside, in addition to this information, the intervention arm assignment. These envelopes will be stored at the study team offices or the clinic and remain sealed until prospective participants are ready to be randomized. Envelopes are not to be opened until a prospective participant is ready to be enrolled and must be used in numeric order.

After the study staff has confirmed that the prospective participant has met all inclusion criteria and none of the exclusion criteria, informed consent has been obtained, and baseline data collection has occurred, the study staff will open the next envelope and assign treatment allocation to the youth participant. The participant's ID number will then be written on the opened envelope. The opened allocation envelope will be retained for documentation in a secure location out of reach of personnel who should remain blind to participants' assignments.

*Blinding*

Since the study participants cannot be blinded to the intervention given that they will be attending peer mentor sessions, primary outcome assessors and data analysts will be blinded. Clinical staff who participate in blood draws and viral load testing will not know participants' study group status. Additionally, study groups will be named "A" and "B" instead of "Intervention" and "Comparison" in the database to avoid bias during the primary analysis.

- B. If human biospecimens (blood, urine, saliva, etc.) will be collected, provide details about who will collect the specimen, the volume (ml) and frequency of collection, how the specimen will be used, stored, identified, and disposed of when the study is over. If specimens will be collected for use in future research (beyond this study), complete the "Biospecimen Repository" section below.

All participants will have blood drawn at three points in the study – baseline for VL and if needed resistance testing, and 6-month and 12-month follow-up for VL testing only. Baseline samples with viral loads of 1000 copies/ml or higher will undergo resistance testing. Trained professionals will collect about 6ml of blood for each viral load and resistance test (a total 12 ml at baseline, 6 ml for the 6- and 12-month follow-up visits each). Blood samples for viral load testing (and resistance testing when applicable) will be collected at all sites, labeled with an ID number, and securely stored at ADCH.

Viral load testing will use the Roche CAP/CTM HIV-1 Test v2.0. The Arthur Davison Children's Hospital lab is a CDC GAP Proficiency monitored lab that routinely performs VL testing in Zambia as part of clinical care.

Laboratory source data will be retained by the laboratory according to local requirements. We will follow local bio-hazardous materials regulations to ensure blood samples are stored in an appropriate repository and are destroyed after the viral load and resistance tests are completed and verified. Resistance testing will be conducted at a qualified lab, such as ADCH, Lancet, University Teaching Hospital (UTH), Center for Infectious Disease Research in Zambia (CIDRZ).

Clinical results (i.e. viral load and resistance test results) will be maintained in participant files at the clinic with participant consent.

- C. If genetic/genomic analyses are planned, address whether the data will be contributed to a GWAS or other large dataset. Address returning unanticipated incidental genetic findings to study participants.

N/A

- D. If clinical or laboratory work will be performed at JHU/JHH, provide the JH Biosafety Registration Number.

N/A

- E. If you will perform investigational or standard diagnostic laboratory tests using human samples or data, clarify whether the tests are validated and/or the lab is certified (for example is CLIA certified in the U.S.). Explain the failure rate and under what circumstances you will repeat a test. For all human testing (biomedical, psychological, educational, etc.), clarify your plans for reporting test results to participants and/or to their families or clinicians. Address returning unanticipated incidental findings to study participants.

Blood samples for viral load resistance testing will be collected at all sites and securely stored at ADCH, labeled with an ID number only. Viral load testing will use the Roche CAP/CTM HIV-1 Test v2.0. The Arthur Davison Children's Hospital lab is a CDC GAP Proficiency monitored lab that routinely performs VL testing in Zambia as part of clinical care. ADCH is also an approved lab for studies like NIH PopART. As such, viral load testing will be performed according to validated SOPs and appropriate quality control measures as practiced by ADCH. In the ADCH lab, the technicians are fully trained and competent in performing VL testing. Laboratory source data will be retained by the laboratory according to local requirements. We will follow local bio-hazardous materials regulations to ensure blood samples are stored in an appropriate repository and are destroyed after the viral load and resistance tests are completed and verified. Resistance testing will be conducted at a qualified lab, such as ADCH, Lancet, University Teaching Hospital (UTH), Center for Infectious Disease Research in Zambia (CIDRZ).

#### *Communicating test results*

Test results from each data collection point (baseline, midline and endline) will be placed in participants' medical files for use by their health care providers. In the introductory meeting of the peer mentoring intervention, participants will review their test results with their health care provider and peer mentor (and interested caregiver, if present). Participants in the maintenance phase will also have opportunities to review their midline VL status with the clinic staff and peer mentor. While all results will be placed in participants' medical files, the study team will make sure that health staff are notified as soon as possible of any participant with viral failure who tests positive for resistance whether they are in the comparison or the intervention arm, so that their ART may be adjusted accordingly.

- F. If your study involves medical, pharmaceutical or other therapeutic intervention, provide the following information: N/A
- Will the study staff be blind to participant intervention status?
  - Will participants receive standard care or have current therapy stopped?
  - Will you use a placebo or non-treatment group, and is that justifiable?
  - Explain when you may remove a participant from the study.
  - What happens to participants on study intervention when the study ends?
  - Describe the process for referring participants to care outside the study, if needed.

